## 8.4 Randomization and Blinding

ObGyn providers will be randomly assigned to one of three study arms based on minimization techniques developed by Pocock and Simon. This minimization approach reduces covariate imbalances by utilizing non-uniform assignment probabilities for the different arms. The study arms will be balanced over the different clinics with equal sampling rates. Providers will be randomized in equal proportions between arms (14 providers per arm). All study personnel, study analysts, and patients will be masked to group assignment. Providers will be unmasked to group assignment. New providers who join a practice after another provider has left will undergo randomization.

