### 1.6 Study Sites Scope of Work

Johns Hopkins' investigators will assume the overall administrative authority and responsibility for regulatory compliance, including reports to the NIH, IRB, and other Johns Hopkins University institutional authorities. Additionally, Hopkins' investigators will: 1) create and implement the electronic medical record changes; 2) enroll all participants; 3) conduct written and oral informed consent procedures; 4) onboard obgyn clinic sites; 5) coordinate focus group and in-depth interviews to obtain feedback from study participants, including providers, patients, and clinic staff; 6) collect field notes; 7) arrange transcription of qualitative methods; 8) quantitative data analysis, including economic analyses; 9) assure quantitative data security and integrity; and 10) write manuscript.

University of Michigan's investigators will: 1) develop the qualitative instruments (i.e., in-depth interview and focus group guides); 2) conduct the focus groups and in-depth interviews virtually; 3) analyze the qualitative data; 4) use the qualitative data to provide feedback to Hopkins' team about the intervention; 5) assure qualitative data security and integrity; 6) train Hopkins' providers to use motivational interviewing techniques; and 7) write manuscript.

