Patients who score medium or high (4-10) will be assigned a study arm based on their provider's group. This will occur automatically via programming integrated into the EHR based on the provider and the type of scheduled visit. The score will be recorded in EHR but it will not be labeled, i.e. a number will be there but nothing about HIV or risk of HIV. This medium/high score group is whom we consider **PrEP-eligible** (e.g., *at substantial HIV risk*) and is the focus of this implementation science study. Based on our preliminary data, we anticipate that a minority of patients (5-10%) will fall into these categories of medium or high risk.

**Clinical trial arms.** The Interventions are guided by the Information-Motivation-Behavior model of behavior change (**Figure 1**).

-Arm 1 Control: standard of care

-Arm 2 Patient-level intervention: patients will be shown a 2.5-minute PrEP animation (information) and their personalized HIV risk messaging (motivation)

-Arm 3 Patient and Provider multi-level intervention: patients will be shown a 2.5-minute PrEP animation (information) and their personalized HIV risk messaging (motivation) AND providers will receive an EHR alert about their patient's personalized HIV risk messaging and a recommendation to offer PrEP. The alert will allow the provider to accept to add the required laboratory tests to start PrEP or decline altogether. Orders will have to be signed by providers but the correct laboratory tests will be ordered to save time and ensure accuracy.

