## **7.4 Fidelity checks**

7.4.1 A research coordinator will observe the implementation of the study at the clinic and take field notes about the workflow, patients' questions, and providers' and stakeholders' concerns. The field notes will be analyzed every six months and used for cost analyses. Additionally, at every 6-month checks, the proportion of consecutive eligible patients who complete the eSHxForm will be assessed per clinic. If

completion is <75%, then research staff will obtain immediate feedback from clinical staff about barriers to completion and devise a plan to increase completion.

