| EFFECTIVENESS                                                                                             | Number of patients who initiate PrEP (primary outcome)                                                                                                                     | Number of providers who document offering of PrEP                                                          | Patient and Providers | EHR chart review                                                                          |
|                                                                                                           |                                                                                                                                                                            | Number of PrEP prescriptions written                                                                       | Providers             | EHR discrete data element                                                                 |
|                                                                                                           | Number of patients who continue PrEP at 3-, 6-, 9- mos                                                                                                                     | Number of PrEP prescriptions written                                                                       | Providers             | EHR discrete data element                                                                 |
|                                                                                                           | Number of patients who are tested for HIV                                                                                                                                  | Number of providers who document offering of HIV test                                                      | Patient and Providers | EHR lab data for HIV testing; EHR chart review                                            |

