|                                                                                                           | QUALITATIVE: What could the team have done better to reach and recruit more providers? What are your perceptions of the training that was offered?                         |                                                                                                            |                       |                                                                                           |
| IMPLEMENTATION                                                                                            |                                                                                                                                                                            | Number of providers who decline the recommendations included in the alert                                  | Provider              | EHR-programmed data transferred directly into RedCap database                             |
|                                                                                                           |                                                                                                                                                                            | Number of clinics that complete assessments in other EHR locations that are not a part of this project     | Clinic                | EHR chart review
Observations, field notes
Checklists                               |
|                                                                                                           | QUALITATIVE: Do you think the interventions were delivered according to plan? What costs (including time and burden, not just money) need to be considered?                |                                                                                                            |                       |                                                                                           |

|             |                                                                                                                                                                                                        |          |                                                                    |

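### Section 8.4 claims masking of all study personnel, which their own tasks rule out, and Table 1 and Section 8.1.1 leave the source of the primary outcome unsettled

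*Protocol*

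**What the plan says.** Section 8.4 makes a blanket statement, "All study personnel, study analysts, and patients will be masked to group assignment", followed by one exception: "Providers will be unmasked to group assignment".

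Other sections assign the tasks and describe the arms:

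- Section 1.6 has the Johns Hopkins investigators "create and implement the electronic medical record changes". Sections 4 and 5.1 say that Epic programming places each patient in an arm according to her provider's group.
- Section 4 describes the arms. The first is "Arm 1 Control: standard of care", with no sham or attention content. In Arms 2 and 3 "patients will be shown a 2.5-minute PrEP animation (information) and their personalized HIV risk messaging (motivation"). Arm 3 adds an EHR alert to the provider.
- Section 7.1.4 plans in-depth interviews with 10-12 providers about how the project is running.
- Section 7.4.1: "A research coordinator will observe the implementation of the study at the clinic and take field notes about the workflow", and also about concerns raised by patients, providers and stakeholders.
- Table 1 (Section 8.0) lists under Implementation "Number of providers who decline the recommendations included in the alert". Section 12.2 has the research team review outcome data and processes every 6 months.

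On the source of the outcome, the Table 1 row "Number of patients who initiate PrEP (primary outcome") gives EHR chart review. The row below it, prescriptions written, gives a discrete EHR data element. Section 8.1.1 defines the primary endpoint as PrEP prescription 4 weeks after the visit.

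**The concern.** A masking statement tells readers which biases the design has controlled. If it claims more than the conduct of the trial allows, the trial is credited with masked outcome assessment that it may not have.

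The practical risk lies in ascertainment. Someone who reads charts for PrEP offers or initiation, and knows that the provider is in Arm 3, may search harder or resolve ambiguous notes differently than for a control provider. The protocol does not say who reads the charts or how they are kept apart from staff who know the arms. The blanket sentence in Section 8.4 is the only stated protection. The risk would reach the primary comparison if the chart-review source in Table 1 were used, and would largely miss it if the discrete prescription field were used. The protocol supports both readings.

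**Working it through.** The point is about consistency, and the protocol gives no figure to reproduce. The check sets the masking statement against each role's tasks, then compares the two definitions of the primary outcome.

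**Step 1. Can each role be masked?**

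| Role | What the protocol has them do or see | Can masking hold? |
|---|---|---|
| Providers | Declared unmasked (8.4) | No, and not claimed |
| EHR build team | Programs the logic linking provider group to patient arm (1.6, 4, 5.1) | No |
| Staff interviewing providers | Discuss delivery with people who know their arm (7.1.4, 8.4) | No |
| Staff handling PrEP-alert responses | The PrEP alert goes to Arm 3 providers only (4, 6.2.2), so a recorded response identifies Arm 3 | No |
| Coordinators observing clinics | Record workflow and providers' concerns (7.4.1) | Unlikely; an inference from the task |
| Patients | See, or do not see, the video and risk message (4) | Not to content; they are not told their assignment |
| Primary-outcome analyst | Can work from coded arm labels | Yes, if the file carries no alert-response field |

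The word *all* therefore fails for at least three groups of personnel. No one need be handed an allocation list for this to happen.

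**Step 2. Which source feeds the primary outcome?**

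| Place | Outcome | Source |
|---|---|---|
| Table 1, row labelled primary outcome | PrEP initiation | EHR chart review |
| Table 1, next row | PrEP prescriptions written | Discrete EHR data element |
| Section 8.1.1 | PrEP prescription at 4 weeks | Not stated there |

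The label sits on one row, and the definition in 8.1.1 matches the other.

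**Step 3. How sensitive is the result to coding?** Section 8.3 gives 1,170 eligible patients and 6% uptake under standard care. Assume an equal split of patients across the three arms.

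- Patients per arm: 1,170 / 3 = 390.
- Expected control events: 0.06 × 390 = 23.4.
- One record coded differently in one arm moves its rate by 1 / 390 = 0.26 percentage points.
- Five records: 5 / 390 = 1.3 points. Ten records: 10 / 390 = 2.6 points.

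For scale, Section 8.3 powers the trial for a difference of 9 points (6% to 15%). The counts of five and ten are assumptions chosen to show a range. Nothing in the protocol says how many records would be affected, and with the discrete field the number should be close to zero.

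**The case against.** The strongest case on the other side is that this is a matter of wording with little consequence for the primary result. Section 8.1.1 and the Protocol Summary both name prescription as the endpoint. Section 11.1 says that the data are mostly clinical data from the EHR, with manual review for some, and Section 12 plans monthly pulls from Epic. The chart-review cell in Table 1 serves a row that also holds documented PrEP offers, so the table does not prove that initiation itself is abstracted by hand. HIV test completion has laboratory data as a listed source. Separation of abstractors may be set out in the site procedures that Section 12 says will be written. All of this stands. It limits the risk but does not make the sentence about personnel true.

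Three stronger readings are tempting, and the protocol does not support them.

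- *Patients know their arm.* A consent waiver is requested, the two disclaimers in Section 13.5.2.1 name no arms, and Section 4 gives Arms 2 and 3 the same patient content. Seeing content differs from knowing the allocation.
- *The co-primary implementation endpoint exists only in Arm 3.* Section 8.1.2 counts providers declining automated orders. Section 3.1.2 speaks of automated HIV test orders, and those are pended for low scorers without reference to arm. Only the Table 1 measure, if it concerns the PrEP alert, is specific to Arm 3.
- *Coordinators are told the allocation.* No section says so. Providers are the randomized unit and arms are balanced over clinics, so being in a clinic does not in itself reveal an arm. Exposure is likely because they record the concerns of unmasked providers in person.

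**Conclusion.** The point holds for personnel. Section 8.4 asserts a property that the protocol's own division of work removes for the EHR build team, for interviewers of providers and for those handling PrEP-alert data, and makes doubtful for clinic observers. For patients the accurate description is *not informed of assignment, and not masked to content*. The source of the primary outcome is also unsettled between Table 1 and Section 8.1.1.

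The size of any bias cannot be derived from the protocol. It is near zero for discrete prescription and laboratory fields. It applies mainly to chart-review measures, chiefly documented PrEP and HIV test offers, and extends to the primary outcome only if initiation is taken from charts. A reader might conclude that the primary comparison is biased; the protocol does not support that, because its stated endpoint can be taken from a field that needs no judgement.

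Two inferences carry part of the argument: that observing and talking with unmasked providers reveals arms, and that arm knowledge could affect how notes are coded. That an alert leaves a visible trace in the chart is possible but not stated, and the conclusion does not need it. The correction should be made because it is cheap and closes an avoidable route for arm-dependent ascertainment.

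**What to change.** 1. **Section 8.4.** Replace the blanket sentence with a statement by role. Not masked: providers, the EHR build team, and staff who observe clinics, interview providers or handle PrEP-alert data. Patients: not informed of assignment. Masked: the analyst of the primary outcome, working from coded arms in a file without alert responses.
2. **Table 1 and Section 8.1.1.** Make them agree that the primary endpoint is PrEP prescription at 4 weeks, taken from the discrete prescription field, and move the primary-outcome label to match.
3. **Remaining chart review (documented PrEP and HIV test offers).** Assign it to existing staff who do not observe clinics and are not given the arm list or the alert log. State openly that full masking may not be possible, since these offers are read from provider notes.

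The cost is protocol wording and some separation of tasks among existing staff. Sample size, randomization and the interventions are unchanged.

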There is no difference between Arms 2 and 3 regarding information and motivation. The difference between these two arms is the provider activity. We are trying to tease apart a clinic-based intervention that targets patients alone (Arm 2) versus both patients and providers (Arm 3). The primary outcome (behavior) is PrEP uptake, and this will be compared based on the Arm the patient is assigned, as is discussed in the data analysis plan. As competing interests (e.g., lack of time) and difficulty assessing the patient's HIV risk consistently have been listed as provider-level barriers to PrEP uptake; and patients do not perceive themselves to be at-risk of HIV, having these two arms will give us a lot of information about how to increase PrEP in women. For instance, Arm 2 will determine whether patients' awareness of their HIV risk will prompt them to ask their provider about PrEP or increase their desire to start PrEP; while Arm 3 will add an additional PrEP facilitator and determine if providers' awareness of their patients' HIV risk level will prompt them to discuss PrEP or increase PrEP uptake by patients.

**Figure 2. Study Schema.** There are two phases in the project. The first is to prepare documents, train staff, enroll providers and clinics. The second includes the clinical trial.

[figure not shown]

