## 8.1 Primary endpoints

**8.1.1** Intervention: Proportion of PrEP prescription 4 weeks after clinic visit

**8.1.2** Implementation Strategy: Proportion of patients who complete the eSHxForm, number of providers declining automated orders (timeframe: q6 months)

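### Section 8.4 unmasks providers in every arm although only Arm 3 has a provider-facing component, so knowing Arm 1 from Arm 2 opens an avoidable route for performance bias in a prescribing outcome

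*Protocol*

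**What the plan says.** Section 8.4 sets the masking rule in two sentences: "All study personnel, study analysts, and patients will be masked to group assignment", and then "Providers will be unmasked to group assignment". The second sentence makes no distinction between arms and gives no reason.

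Section 4 defines the arms. The control is "Arm 1 Control: standard of care". Arm 2 is a short PrEP animation and a personalised risk message, both shown to the patient. Arm 3 adds an EHR alert to the provider, with a recommendation to offer PrEP and the laboratory orders ready to sign. On how medium- and high-scoring patients receive their arm, Section 4 says "This will occur automatically via programming integrated into the EHR based on the provider and the type of scheduled visit". On Arms 2 and 3 it says "The difference between these two arms is the provider activity", and it gives the purpose as separating an intervention aimed at patients alone from one aimed at patients and providers.

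The primary effectiveness endpoint in Section 8.1.1 is "Proportion of PrEP prescription 4 weeks after clinic visit". Table 1 lists prescriptions written as a provider-level measure.

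**The concern.** The person who produces the primary outcome is allowed to know the allocation in two arms where no procedure requires it. Arm 2 is meant to show what happens when only the patient is prompted. An Arm 2 provider who knows her arm also knows that her medium- and high-scoring patients are being shown PrEP information, and that is a general provider-level cue. An Arm 1 provider who knows she is a control may compensate by raising PrEP more often, or may disengage.

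Objective 3.1.1 is at stake: which of the two interventions does more for PrEP uptake. If awareness of the arm changes prescribing, Arm 2 versus Arm 1 no longer reflects patient messaging alone, and Arm 3 versus Arm 2 no longer compares the alert with a provider who has no cue.

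The protocol accepts this kind of mechanism. Section 5.1 randomises providers, and not patients, so that a provider exposed to an intervention does not unconsciously carry it over to control patients.

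**Working it through.** **1. Does anything in Arms 1 and 2 require the provider to know her arm?**

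| Element | Where | Arms | Requires knowledge of arm in Arms 1 and 2? |
|---|---|---|---|
| Motivational interviewing training | 5.3, 7.1 | all | no |
| Provider PrEP animation | 6.3, 7.1.3 | all | no |
| eSHxForm and arm assignment by Epic | 4, 5.1 | all | no |
| Patient animation and risk message | 4 | 2 and 3 | no, shown to the patient |
| Provider alert | 4, 6.2.2 | 3 only | not applicable; it reveals Arm 3 by itself |

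**2. How many providers and patients are involved?** Inputs are 42 providers, 14 per arm (8.4), and 1,170 eligible women (8.3).
- Providers in Arms 1 and 2: 2 × 14 = 28, and 28/42 = 67%.
- Women: 1,170/3 = 390 per arm, so 2 × 390 = 780.
- At the plan's 6% uptake, one arm yields 0.06 × 390 = 23.4 prescriptions. One percentage point is 3.9 prescriptions, or 3.9/14 = 0.28 per provider over the whole trial.

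**3. Where would the bias enter?** Let *m* be the effect of patient messaging and *v* the effect of adding the alert, both measured against providers who do not know their arm. Let *a1* and *a2* be the changes in prescribing caused by knowing one is in Arm 1 or Arm 2. On an additive scale:
- Arm 2 − Arm 1 = *m* + (*a2* − *a1*)
- Arm 3 − Arm 2 = *v* − *a2*

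If providers without the alert cannot tell Arm 1 from Arm 2, they share one shift *a0* (they can infer only that they are not in Arm 3). It cancels in Arm 2 − Arm 1. It does not cancel in Arm 3 − Arm 2, where the gain is less certain.

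**4. Scale, under assumed shifts.** The document gives no value for *a1* or *a2*, so the shifts below are assumptions. Take n = 390/1.27 = 307.1 effective women per arm (design effect from 8.3) and two-sided alpha 0.05, which is also assumed because 8.3 states none:

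power = Φ{ [ |p2 − p1|√n − 1.96√(2p̄(1 − p̄)) ] / √(p1(1 − p1) + p2(1 − p2)) }

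The plan's own contrast first, 6% versus 15%: (0.09 × 17.52 − 1.96 × 0.4335)/0.4288 = 1.70, so power is 95.5%. Section 8.3 states 80%. That mismatch is a separate matter and does not bear on this point.

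- *Messaging has no effect, and awareness alone raises Arm 2 above 6%.* The chance of a significant result favouring Arm 2 (nominal 2.5%) is 7% for +1 point, 16% for +2, 29% for +3 and 60% for +5.
- *Arm 2 is truly at 15%, and awareness moves the control rate.* Power is 99.7% with control at 4%, 98.6% at 5%, 95.5% at 6%, 88.8% at 7%, 77.7% at 8% and 62.9% at 9%.

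The two cases pull in opposite directions. They show how the comparison responds to a shift; they do not estimate one.

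**5. Does the planned analysis deal with it?** Section 8.5 analyses by assigned arm, with provider and patient random effects and adjustment for demographic imbalance. None of these removes behaviour caused by the assignment itself. The analysis of PrEP uptake in low-risk patients looks for general spillover. It does not isolate awareness among the medium- and high-risk women in the primary comparison.

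**The case against.** The strongest reply has four parts.

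*Unmasked is not the same as told.* No visible section describes notifying Arm 1 or Arm 2 providers, and the provider consent form is not available for review. The sentence may only decline to claim provider masking. This stands as a caution, but the rule as written permits disclosure in every arm, so it should be narrowed.

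*Masking would leak through the mechanism under test.* Section 4 expects Arm 2 patients to ask about PrEP, and a provider who never sees an alert can rule out Arm 3. This stands: masking would be partial, and weakest where Arm 2 works best. Still, learning from an occasional patient gives a provider less than knowing her arm from the start.

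*The cue is weak.* Knowing one's arm does not show which patients saw the message. More than 90–95% of patients are expected to score low, and the score carries no risk label (Section 4 is itself inconsistent on whether it is visible in the EHR). Arm 3 supplies a patient-specific risk level, a recommendation and orders. Much of the intended contrast therefore survives, and comparing strategies with clinicians aware of them is defensible in a hybrid effectiveness-implementation trial. This limits the concern but does not explain why Arms 1 and 2 must be distinguishable.

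*There are partial checks.* Table 1 records, by chart review, providers who document offering PrEP. Section 8.5 looks at low-risk patients and at attenuation over time. Prescriptions are discrete EHR data and analysts are masked, so biased ascertainment is limited. These checks help to detect a change in provider behaviour but do not remove it.

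**Conclusion.** The point holds as an avoidable risk of performance bias in Arm 2 versus Arm 1, and possibly in Arm 3 versus Arm 2. It rests on three facts in the text: unmasking is not limited by arm, Arms 1 and 2 have no provider component, and the provider writes the primary outcome. It concerns 28 of 42 providers and about 780 of 1,170 eligible women.

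A reader might infer more, and the document does not support it:
- It does not show that the patient-only effect is confounded. Allocation is randomised; the issue is behaviour after allocation.
- It does not show that some stated share of the 6% to 15% contrast is lost. Size and direction are both unknown. Control providers could compensate or disengage, and the Arm 3 versus Arm 2 difference is understated only if awareness raises Arm 2 prescribing.
- It does not show that the protocol contradicts itself. Unmasking is a design choice, and a better one is available at little cost.

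**What to change.** Revise Section 8.4 along these lines: *Arm 3 providers will know their assignment through the alert. Providers who do not receive the alert will not be told whether they are in Arm 1 or Arm 2.* Align the provider consent by describing all three arms without disclosing the individual allocation.

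The cost is wording in 8.4 and in the provider consent. Sample size, Epic programming and analysis do not change. The downside is incomplete masking, since Arm 2 patients may mention the animation or ask about PrEP, and Section 8.4 should say so. Asking Arm 1 and Arm 2 providers to guess their arm at study end is optional and hard to interpret, because a correct guess may simply mean that the intervention worked.
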